## Abstract

**Background:**

Current guidelines recommend education, physical activity and changes in diet for type 2 diabetes patients, yet the composition and organization of non-pharmacological care are still controversial. Therefore, it is very important that programmes aiming to improve non-pharmacological treatment of type 2 diabetes are developed and evaluated. The Copenhagen Type 2 Diabetes Rehabilitation Project aims to evaluate the effectiveness of a new group-based lifestyle rehabilitation programme in a Health Care Centre in primary care.

**Methods/Design:**

The group-based diabetes rehabilitation programme consists of empowerment-based education, supervised exercise and dietary intervention. The effectiveness of this multi-disciplinary intervention is compared with conventional individual counselling in a Diabetes Outpatient Clinic and evaluated in a prospective and randomized controlled trial. During the recruitment period of 18 months 180 type 2 diabetes patients will be randomized to the intervention group and the control group. Effects on glycaemic control, quality of life, self-rated diabetes symptoms, body composition, blood pressure, lipids, insulin resistance, beta-cell function and physical fitness will be examined after 6, 12 and 24 months.

**Discussion:**

The Copenhagen Type 2 Diabetes Rehabilitation Project evaluates a multi-disciplinary non-pharmacological intervention programme in a primary care setting and provides important information about how to organize non-pharmacological care for type 2 diabetes patients.

**Trail Registration:**

**ClinicalTrials.gov **registration number: NCT00284609.

## Background

Type 2 diabetes mellitus (T2DM) is a chronic disease with severe late complications and high mortality. The increasing prevalence of T2DM is mainly due to reduced physical activity and consumption of unhealthy food and larger portion sizes in genetic susceptible individuals. Lifestyle intervention can prevent development of T2DM in subjects with impaired glucose tolerance [1,2]. To improve metabolism and reduce the risk of late complications of T2DM, permanent changes in lifestyle and lifelong multi-pharmacological treatment are needed [3].

Group-based lifestyle intervention programmes for T2DM patients, including patient education or supervised exercise, have been evaluated in several randomized controlled trials. Education programmes alone improves glycaemic control in some studies [4,5], but not in all [6]. Group-based diabetes education seems to have a better effect on glycaemic control than individual education [7-10]. However the studies and interventions included in these meta-analyses are very heterogeneous.

Isolated aerobic exercise [11], resistance training [12], and the combination of these[13] resulted in better glycaemic outcomes compared with the control groups. Exercise in groups (exercise period ranging from 8 weeks to 12 month) lowered HbA1c approximately 0.6 percentage points [14,15].

Dietary advice is an accepted cornerstone of treatment for T2DM, but no quality data on the efficacy of diet intervention per se on glycaemic control, reduction in body weight, development of diabetic complications or quality of life exists for the treatment of T2DM [16].

It is still an open question whether group-based or individual lifestyle intervention programmes gives the best glycaemic control, whether exercise interventions have a long term effect and finally whether lifestyle changes can improve long term results of T2DM treatment.

A new health care centre is established at Oesterbro in eastern Copenhagen as a result of a local collaboration project between the City of Copenhagen, Bispebjerg University Hospital and general practitioners [17]. The health care centre is planned to be responsible for lifestyle rehabilitation of patients with one or more of four selected chronic conditions – type 2 diabetes, chronic obstructive pulmonary disease, chronic heart failure and older patients with balance problems. A new rehabilitation programme combines empowerment-based education, exercise training and dietary advice on a group-based level as one multi-disciplinary intervention.

The aim of the current study is to compare the metabolic, physiological and psychological effects of this new group-based multi-disciplinary lifestyle rehabilitation programme for T2DM patients in a primary care setting with an individual counselling programme in a diabetes outpatient clinic. We hypothesize that patients participating in the group-based rehabilitation programme including supervised exercise will improve their glycaemic control, self-rated diabetes symptoms and quality of life significantly more in the short and long term than patients receiving conventional individual advice on changes in lifestyle.

## Methods/design

### Patient recruitment and randomization

We plan to recruit patients through advertisements in local newspapers, pharmacies and from the outpatient clinic at Bispebjerg University Hospital, and by letters and e-mails to general practitioners inviting them to refer patients to the study (Figure 1). Key inclusion and exclusion criteria are shown in Figure 2. Diagnosis of T2DM is defined according to the criteria of WHO [18]. Patients willing to participate will be screened after written informed consent is obtained, and those fulfilling the inclusion criteria will be randomised within three weeks, stratified by gender and age (18–54 years and ≥ 55 years). A person not participating in the study creates a randomization list, and the randomization is done at the baseline visit using consecutively numbered sealed envelopes. Patients will be randomised to a group-based rehabilitation programme (intervention group) at the Health Care Centre Oesterbro or to an individual counselling programme (control group) in the Diabetes Outpatient Clinic, Bispebjerg University Hospital.

**Figure 1 F1:**
[figure not shown]
**Flow-chart of events in the study**. From recruiting patients through randomization and follow-up.

**Figure 2 F2:**
[figure not shown]
**Key inclusion and exclusion criteria**.

#### Intervention group

Lifestyle rehabilitation at Health Care Centre Oesterbro consists of a multi-disciplinary intervention including three programmes (Figure 3).

**Figure 3 F3:**
[figure not shown]
**The group-based rehabilitation programme outline**.

**The education programme **consists of one weekly group session of 90 minutes for 6 weeks, limited to 8 patients per group. A nurse, a physiotherapist, a dietician and a podiatrist run the sessions. The education programme is originally developed at the diabetes outpatient clinic, Bispebjerg University Hospital, and focuses on achievement of self-selected goals, psychosocial adaptation, enhanced control and problem solving strategies [19]. The programme is modified and adjusted to a multi-disciplinary education team, and the contents of the sessions include information on the pathophysiology of diabetes; the role inheritance and environment; education in self blood-glucose monitoring; the importance of physical activity, healthy diet, weight loss, medication, and smoking cessation; the late complications of T2DM; hypertension and cardiovascular disease. The podiatrist advises patients about foot care and examines the patients' feet. The empowerment approach to diabetes education involves patient collaboration and seeks to increase the patients' knowledge and self-awareness, which enables them to take charge of their own diabetes self-management [20].**The diet instruction programme **consists of two 3-hours group-based cooking courses and 1 session in a local supermarket [21]. Patients' spouses are encouraged to join the cooking courses.

**The physical exercise programme **is supervised and is 90 minutes in duration and sessions take place twice a week for 12 weeks. The sessions are group-based, but a physiotherapist tailors an individual exercise programme for each patient including both aerobic and resistance exercise [22]. After initial measurement of blood-glucose levels, the patients start the warm-up exercise for 20 minutes. This is followed by basic exercise training for 15 minutes, followed by aerobic exercise on a bicycle ergometer for 12 minutes, resistance training (seated leg press, chest press, pull down and leg extension) for 25 minutes, stretch for 10 minutes, followed by a final blood-glucose measurement. The patients are advised to perform 30 minutes of physical activity on at least three additional days per week according to international guidelines [23]. In addition patients are offered an optional **smoking cessation course **if needed.

Before patients enter the programme they participate in an individual motivational interview with a nurse or a physiotherapist. The personnel are educated and continuously supervised in the use of the motivational interviewing technique by a specialized psychologist [24]. The patients set personal goals, and these goals are evaluated after the intervention programme at a final consultation and 1 and 3 months later by telephone follow-up contacts.

The teams from the health care centre and from the diabetes outpatient clinic meet on a regular basis to share knowledge and to ensure a common understanding of care and agreement on the components of the programmes in the two organizations.

### Control group

On the basis of the same empowerment approach the lifestyle intervention at the Diabetes Out-patient clinic at Bispebjerg Hospital includes four monthly 1-hour sessions of individual counselling with a diabetes nurse specialist [19,20] (Figure 4). The nurse is educated in the use of the motivational interviewing technique and has a bachelor degree in education. Using storytelling patients are given information about diabetes in general, medication, risk factors and late complications of T2DM. They receive guidance in self-monitoring of blood-glucoses and on how to increase their level of physical activity.

**Figure 4 F4:**
[figure not shown]
**Individual outpatient counselling programme outline**.

The programme also includes three individual counselling sessions with a dietician, who is also educated in the use of the motivational interviewing technique[24]. The patients' set personal goals and the dietician develops in cooperation with the patient, a diet-schedule based on biochemical, anthropometrical and medical records including patients' motivation and attitudes. The schedule and goals are evaluated at two 30-minute follow-up visits.

The patients receive 45 minutes guidance and instructions about foot-care from a podiatrist. Finally patients are offered an optional smoking cessation course if required.

### Pharmacological treatment

Both intervention programmes are non-pharmacological. The endocrinologist or the general practitioner treating and monitoring the patients prior to the study continue as the patients' physician (disease manager) during and after the intervention. Recent guidelines on pharmacological treatment are followed [25]. The study does not include changes in principles for the pharmacological treatment. Patients are asked to report any alternation in their medication and these will be quantified by the study investigator and used in the analyses as a covariate.

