### Biochemical measurements

Blood and urine samples are taken in the morning after an overnight fast. Plasma glucose, lipids, C Reactive Protein, creatinine and urine albumin/creatinine ratio are analysed at the Department of Clinical Biochemistry, Bispebjerg University Hospital. Haemoglobin A1c is measured on venous whole blood samples in K2-EDTA tubes at the Department of Clinical Biochemistry, Steno Diabetes Centre [28]. Blood samples for serum C-peptide, insulin and proinsulin are centrifuged for 10 min at 3000 rpm, at 20°C immediately after sampling, and serum is isolated and frozen before analysis at the Steno Diabetes Centre. Blood samples for later analyses will be centrifuged within 60 minutes of sampling and stored frozen at -20°C. The target for haemoglobin A1c is below 6.5% according to international guidelines [27].

The Homeostasis Model Assessment (HOMA) is used to estimate insulin resistance and beta-cell function [29]. HOMA-IR is computed as follows: fasting insulin (μU/ml) × fasting glucose (mmol/L)/22.5. HOMA-B is calculated using the following formula: 20 × fasting insulin (μU/ml)/fasting glucose (mmol/L) – 3.5.

Microalbuminuria is defined as a urine Albumin:Creatinine Ratio (ACR) ≥ 2.5 – 25 mg/mmol in men and ≥ 3.5 – 25 mg/mmol in women [30]. Treatment targets for blood lipids are values of fasting total cholesterol below 4.5 mmol/L and fasting LDL cholesterol below 2.5 mmol/L [31].

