### Sample size considerations and statistical methods

The size of the study population is based on the primary outcome measure HbA1c and is estimated on the basis of the results of two meta-analyses relating to education and exercises in T2DM patients [8,14]. According to power calculation, an absolute difference of 0.7% in HbA1c between the groups (power 0.9, significance level 0.05) may be detected with 80 patients in each group. This calculation is based on a standard deviation of the HbA1c-value of 1.3 from larger population studies [40].

Neither patients nor study personnel are blinded to treatment assignment. The study statistician carrying out the data analysis on the primary and secondary outcomes will be blinded and will not have any contact with the patients.

Descriptive statistics (means ± SD, or median and interquartile ranges, as appropriate) will be used to describe the study sample with regards to baseline characteristics. The analysis will be performed according to the intention-to-treat principles using the statistical software SAS 9.1. Comparisons of primary and secondary outcomes between the two groups will be analyzed by values after the intervention at the 6 months follow-up visit, and 12 and 24 months after baseline, using appropriate parametric tests for variables fulfilling the normal distribution criteria or appropriate non-parametric tests for variables not fulfilling the normal distribution criteria. Sensitivity analyses will be carried out with adjustment for possible confounders. When relevant the change in outcomes from baseline to 6, 12 and 24 months follow-up will be assessed. The proportion of patients reaching the recommended goals for glycated haemoglobin, blood pressure and lipids will be compared in a sub-analysis. Statistical significance is set at P < 0.05.

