## Discussion

This prospective, controlled and randomized open label study tests the hypothesis that a new multi-disciplinary group-based lifestyle intervention programme for T2DM patients in a primary health care setting results in better short- and long-term glycaemic outcomes than the traditional best practice for individual lifestyle counselling in a diabetes outpatient clinic setting. The major difference between the two interventions is that the new rehabilitation programme includes a supervised exercise programme, whereas the control group receives advice regarding physical activity. The content and the principles of empowering patients are the same in the two interventions, but the education programme in the health care centre is group-based.

The evidence of the beneficial effects of exercise on diabetes symptoms, physical fitness and quality of life in T2DM is strong [41], and previous group-based non-pharmacological lifestyle studies show improvement in glycaemic control and weight loss compared to individual counselling [9]. Most lifestyle intervention studies have been focused mainly on education, including advice on physical activity and diet, or on exercise training and/or diet. Only a few randomized controlled trials have investigated interventions incorporating several elements of non-pharmacological treatment of T2DM including patient education, supervised exercise and dietary advice on a group-based level [42-45]. However, the number of patients, follow-up time and effects on glycaemic control were very heterogeneous in these studies. It is very important in T2DM management programmes to find ways to increase the impact of non-pharmacological treatment in T2DM patients. Our study may add further evidence to this.

The lifestyle rehabilitation programme is multi-disciplinary including group-based education, dietary advice and exercise, and it is not possible to extract the individual effects of each component. The interventions are non-pharmacological, but the patients are urged to continue their medication throughout the study since the clinical effects of a multi-pharmacological treatment on late diabetic complications are highly significant [46]. Decisions on changes in medication are left to the discretion of the patients' physicians, who are not part of this study.

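### Medication changes made after randomisation are to enter the analyses as a covariate, and the plan does not keep them out of the primary HbA1c comparison

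*Protocol article*

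**What the plan says.** All references are to the protocol article.

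- **Pharmacological treatment.** Each patient's existing endocrinologist or general practitioner will "continue as the patients' physician (disease manager) during and after the intervention", treating according to current guidelines. Patients report changes in their drugs, and "these will be quantified by the study investigator and used in the analyses as a covariate". No particular analysis is named.
- **Discussion.** "Decisions on changes in medication are left to the discretion of the patients' physicians, who are not part of this study".
- **Biochemical measurements.** The HbA1c target is below 6.5%.
- **Outcome measures and data collection.** HbA1c is the primary outcome, measured at baseline and at 6, 12 and 24 months.
- **Sample size considerations and statistical methods.** The analysis follows intention-to-treat. The arms are compared at each follow-up visit by parametric or non-parametric tests according to distribution, with no covariate named. Separately, "Sensitivity analyses will be carried out with adjustment for possible confounders"; the confounders are not listed. On masking, "Neither patients nor study personnel are blinded to treatment assignment", although the statistician who analyses the primary and secondary outcomes is blinded.

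**The concern.** Medication change is measured after randomisation. Under guideline care with an HbA1c target, a patient whose HbA1c stays high is more likely to have treatment intensified, and a programme that lowers HbA1c should make this less frequent. The covariate is therefore partly an effect of the assigned arm and partly an effect of the outcome process.

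Two things follow if it is put in a regression. Part of the programme's effect can be adjusted away or added to. Confounding by indication also enters, because the patients who changed drugs are those who were doing worse. The coefficient for arm then answers neither of the two natural questions: the effect of offering the programme under usual prescribing, or the effect had no drugs been changed.

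The trial's main claim is about glycaemic control. If the covariate rule may or may not apply to the primary outcome, the choice can be made after the results are known.

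**Working it through.** **1. The two sections side by side.** The pharmacological section commits to the covariate in the analyses without limit. The statistics section describes main tests without covariates and places adjustment in sensitivity analyses, but does not mention medication. Two readings are open:

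- (a) the covariate belongs only to the sensitivity analyses;
- (b) it also enters the main comparison.

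Nothing in the article excludes (b).

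**2. Is medication change a confounder?** A confounder of the arm comparison must influence, or share a cause with, the assignment. Assignment is random and comes first, so a later drug change cannot do so. This holds under both readings.

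**3. The plan's own figure.** With difference 0.7, SD 1.3, power 0.9 and two-sided 0.05 (sidedness assumed), n = 2 × (1.960 + 1.282)² × 1.3² / 0.7² = 72.5, so 73 per group (74 by the t test). The plan states 80, which is on the safe side (power 0.92 to 0.93). The point does not depend on this figure.

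**4. Illustration.** From the protocol: SD 1.3 and a programme effect of −0.7 (the planning difference). Everything else is assumed. Arm is A, persistent severity B ~ N(0,1), and e is independent N(0,1) noise at each time:

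- drug-free HbA1c at an interim time and at the end, as deviations: H = 1.3 × (√0.8 × B + √0.2 × e) − 0.7A;
- medication intensified (M = 1) with logit P = −1 + s × H(interim);
- observed HbA1c: Y = H(end) − d × M.

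Y was regressed on arm, with and without M and with and without baseline HbA1c, in 2,000,000 simulated patients. The Monte Carlo error of the simple contrast is about 2 × 1.3 / √2,000,000 = 0.002. Negative values favour the programme.

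| Drug effect d | Slope s | M, control / intervention | Arm only | Arm + M | Arm + baseline | Arm + baseline + M |
|---|---|---|---|---|---|---|
| 0 | 1 | 0.319 / 0.214 | −0.699 | −0.588 | −0.700 | −0.674 |
| 0 | 2 | 0.375 / 0.223 | −0.701 | −0.483 | −0.700 | −0.642 |
| 0.5 | 1 | 0.319 / 0.214 | −0.643 | −0.585 | −0.645 | −0.673 |
| 0.5 | 2 | 0.375 / 0.223 | −0.621 | −0.479 | −0.625 | −0.643 |
| 1.0 | 1 | 0.319 / 0.213 | −0.596 | −0.591 | −0.595 | −0.675 |
| 1.0 | 2 | 0.374 / 0.223 | −0.546 | −0.480 | −0.546 | −0.640 |

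- **Without baseline HbA1c,** adding M moves the estimate toward zero, by 0.596 − 0.591 = 0.005 up to 0.701 − 0.483 = 0.218. Power at 80 per group is 0.85 to 0.93 without M and 0.75 to 0.86 with it.
- **With baseline HbA1c,** the shift goes both ways: toward zero by up to 0.700 − 0.642 = 0.058, and away from zero by up to 0.640 − 0.546 = 0.094.
- **In no row** does a model with M recover the drug-free −0.70.
- **Confounding by indication is visible.** With d = 0.5 and s = 1, the drug lowers HbA1c by 0.5, yet the fitted coefficient of M is +0.55 without baseline HbA1c and −0.26 with it.
- **With s = 0** (prescribing unrelated to HbA1c or arm), the gap is 0.

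**5. No programme effect and no drug effect.** If prescribing depends on HbA1c alone (s = 1), adjustment does no harm: the estimate is 0. If arm also changes the log-odds of intensification directly by −1 or +1, the adjusted difference is +0.154 or −0.187, while the unadjusted one stays at 0 within 0.002. That direct influence is assumed.

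**The case against.** The strongest reply is that the primary test is probably untouched. The statistics section compares follow-up values by simple two-group tests and mentions adjustment only for sensitivity analyses. Those are among the analyses, so the sections do not strictly contradict each other, and a covariate in a sensitivity model does not breach the intention-to-treat commitment. This stands as far as it goes: a reader might infer that the primary result is certainly biased, and the article does not support that. But it does not exclude the other reading, and even on the favourable one, adjustment for medication change would be wrongly described as control of confounding.

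Second, drug changes can mask a programme effect, so looking at them is legitimate. That also stands. With baseline HbA1c in the model and a drug effect of 0.5 or 1.0, the adjusted value lies nearer the drug-free effect than the total effect does. It still misses it, and with no drug effect it lies further away. The question deserves its own method.

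Third, a reader might take the largest simulated shift, about a third of the 0.7 planning difference (0.218 / 0.7 = 0.31), as the expected bias. It is not. Most inputs are assumed, and that value arises only in a model without baseline HbA1c and with steep, HbA1c-driven prescribing. The spurious differences under no effect need prescribing to differ by arm for reasons other than HbA1c. The article states no such difference: the same physicians continue in both arms under the same guidelines.

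Fourth, self-reported changes scored by an unblinded investigator suggest arm-aware scoring. The open design is documented; biased scoring is not. Blinding the statistician does not protect a score assigned earlier, but nothing in the article allows an effect to be estimated.

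**Conclusion.** The point holds in a limited form. The article states a rule, adjustment for medication changes made after randomisation, that would give the wrong comparison if applied to the primary outcome and would be mislabelled if applied as confounder control elsewhere. This is a stated commitment, not a detail left to a fuller document. Whether it reaches the primary test is open, because the two sections are not tied together.

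Size and direction cannot be derived from the documents. Shifts of roughly 0 to 0.2 HbA1c points, toward or away from zero depending on the model, are illustrations that rest on the assumed prescribing slope, drug effect and correlation of HbA1c over time. The shift disappears if prescribing depends on neither HbA1c nor arm, which is implausible with guideline care and an HbA1c target.

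**What to change.** Reconcile the two sections before any outcome data are analysed by arm:

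- Replace the covariate clause in the pharmacological section with wording such as: *Reported medication changes will be summarised and compared by arm. The primary HbA1c comparison includes patients as randomised, whatever changes in medication occur, and any covariate in it is measured at baseline. An analysis that accounts for medication change is supplementary, and its question and method are stated in advance.*
- Name the baseline covariates, if any are used: for example baseline HbA1c, baseline medication and the randomisation strata (gender and age group). State in the statistics section that variables arising after randomisation do not count as possible confounders.
- If an effect without drug changes is wanted, define it and choose a method suited to it. One example is to set HbA1c values after a change to missing and multiply impute them under stated assumptions.
- Optional: score medication changes from lists that do not show the arm.

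The cost is a few sentences and slightly more analysis work, with no added patients or visits. The sponsor gives up a medication-adjusted headline result.
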